***Recruitment and randomisation***

We will recruit 50 schools across central and southern England. As with our previous trials, schools will be recruited by a combination of emails and phone calls to schools, local authorities, school networks and academy chains, as well as a recruitment event and visits. Recruitment materials will indicate Positive Choice’s alignment with but greater coverage than statutory guidance plus its alignment with Ofsted criteria and safeguarding guidance. Response rates will be recorded, as will any stated reasons for non-participation. After baseline surveys with students in term 2 of year 8 (November 2021-March 2022), schools will be randomly allocated 1:1 to intervention/ control as a single batch remotely using a random number generator by LSHTM clinical trials unit (CTU), stratified by school-level GCSE attainment and local index of deprivation, which are key predictors of sexual health.(49) Schools will be given unique study numbers to preserve allocation concealment within the CTU. The fieldwork team will be informed of allocations and inform schools. Informed by the pilot and previous studies and in line with the ‘If I Were Jack’ RCT,(54) we will incentivise recruitment and retention by offering a £500 payment to all schools with an additional £1000 for those allocated to the intervention group and a further £500 for case study schools, reflecting the greater research load on such schools. Our pilot and other studies suggest that payment is now absolutely essential for maintaining school participation in research.(42, 53) Each school will also be allocated a named research liaison contact to facilitate retention.

***Intervention and comparator***

Positive Choices is a whole-school intervention with the following components informed by the Safer Choices, Children’s Aid Society Carrera and Gatehouse interventions:

1) School health promotion council comprising a diverse group of 6 staff (including RSE/Personal, Social, Health and Economic Education (PSHE) coordinator and senior leadership team members) and 6 students (diverse by school engagement and gender, inclusive by sexual orientation), which meets termly to plan, launch, coordinate and oversee delivery of components 3-6. Each school nominates an intervention champion (senior leadership team member) and a day-to-day intervention lead (RSE/PSHE coordinator) both of whom will sit on the school health promotion council, an approach successfully used in other secondary school interventions.(59)

2) A student needs survey of year-8 students (age 12/13; drawing on the baseline RCT survey) which identifies areas of need overall (e.g. specific knowledge gaps, risk behaviours) and by student subgroups including disadvantaged and sexual/gender-minority students, and provides evidence to help the school health promotion council build school commitment to the work and inform local tailoring of intervention components 3-6.

3) A classroom curriculum addressing social and emotional skills and relationships and sexual health knowledge and skills, delivered by school staff to increase scalability and sustainability. The curriculum is designed as a set of learning modules, some of which are delivered in all schools (8 lessons for year 9; 5 for year 10) and some of which are ‘add-on’ lessons, with schools choosing from a menu of lessons based on assessed student needs (2 for year 9; 1 for year 10) providing 10 hours for year 9 and 6 hours for year 10 in total. For year 9, essential lessons are: a) the female/male body and reproductive organs; b) fertility and contraception; c) STIs and safer sex; d) building blocks to good relationships; e) consent; f) sustaining relationships; g) sexual response and pleasure; and h) pornography. ‘Add on lessons’ are: i) pregnancy options; ii) readiness for intimacy; iii) body image and the digital world; iv) female genital mutilation; and v) human rights, stigma and discrimination. Overall, provision will align with statutory requirements.

4) Student-run social-marketing campaigns facilitated by trained teachers and formulated and implemented by 12-18 students per school, diverse by gender and school engagement aiming to appeal to a diversity of students including disadvantaged and sexual/gender-minority students. Campaigns use social and other media, posters and events, and focus for example on healthy relationships, sexual rights, DRV and/or access to local services, with at least one campaign being delivered per year.

5) Parent information – three newsletters and two homework assignments per year addressing parent-child communication.

6) Review of school and other local sexual and reproductive health services to inform improvements in provision and/or access.

Delivery of these components is supported by SEF providing schools with the following: a 1/2-hour start-up meeting with each school’s senior leadership team and RSE coordinator to build commitment and enable timetabling and staffing; train-the-trainer sessions for selected school staff delivered via a blend of a total of 7-hour face-to-face (for curriculum) and 2-hour online (for social marketing) training per year (video-recorded so that schools may use recordings as an internal training resource); a manual; materials for staff training, the curriculum and parent information; and guidance for the social-marketing campaigns and sexual and reproductive health services review (all materials will be downloadable via a password-protected website). Curriculum training is then cascaded to classroom teachers in 1-3 hour internal trainings per year arranged over multiple sessions to suit each school. Teachers delivering the curriculum will also have access to regular webinars and drop-in sessions with SEF staff to support delivery. The intervention aims to: modify some existing provision (RSE curriculum for years 9 and 10; parent information; access to local health services); as well as providing new activities (school health promotion council; needs survey; social-marketing campaigns).

Positive Choice’s programme theory is informed by social marketing, and has been developed with experts in this field, addressing the 4 ‘P’s,(60, 61) ‘selling’ consumers a **P**roduct *they* want (holistic RSE based on expressed consumer needs) in an accessible **P**lace (school) at a low **P**rice (free to students), with **P**romotion by and to peers and to parents (campaigns, parent information), addressing competing influences from peers, media etc.(62) Positive Choices is also informed by social influence(63) and social cognitive theories(64) to address the following determinants of sexual and reproductive health including DRV: relationships/sexual health-related knowledge, skills and communication self-efficacy; attitudes about gender and DRV; social norms about healthy relationships (all via the curriculum and social marketing); and sexual health communication with parents (via parent information). It is also informed by the social development model,(65) with student participation in school health promotion councils and social-marketing campaigns theorised to increase school engagement, and positive career and educational aspirations,(66) which are associated with better sexual health.(67) Review of school-based and local sexual and reproductive health services is theorised to improve access in line with NICE guidance.(68)

Control schools will continue with existing RSE/sexual health provision, to be described via the process evaluation to maximise the external validity of the trial to assessing the intervention against normal provision in schools in England. Our pilot reported that schools varied in what was delivered but did not offer interventions components comparable to Positive Choices. Control schools will be informed by new statutory guidance on relationships, sex and health education. Compared to this statutory guidance, Positive Choices is more comprehensive in its coverage and much more focused on developing skills and self-efficacy etc. and not merely knowledge. The new statutory guidance refers to whole-school approaches but does not suggest specific activities whereas Positive Choices includes school health promotion councils, needs surveys, student-run social marketing and review of sexual and reproductive health services. Hence, there will be a very clear distinction between intervention and comparator.

***Outcome measures***

These will be assessed via self-reports at 33 months (age 15/16). All of our outcome measures have been piloted successfully in our pilot RCT and other studies (ordinal alphas for multi-item scales reported below).(42, 53)

Our primary outcome will be a binary measure of non-competent first sex. This measure has been chosen because it: provides the best measure of overall sexual health in this age-group regardless of gender or sexual orientation; is strongly associated with multiple adverse sexual health outcomes including STIs, non-volitional sex, unplanned pregnancy and sexual dysfunction;(1) was recommended through PPI with policy stakeholders and young people; is appropriate given the intervention now includes DRV prevention; and is sufficiently prevalent among trial participants to provide statistical power through a pragmatic sample size.(1, 2) It has been recommended as an impact measure by the World Health Organisation, is sensitive to intervention effects and is starting to be used in evaluations.(69, 70) Non-competent first sex will be assessed among trial participants having sex for the first time between baseline and follow-up, using the established Natsal self-report measure defined in terms of the absence at first sex of: autonomy of decision; equal willingness of partners; its being the ‘right time’; and, for those reporting heterosexual intercourse, use of effective contraception.(1, 2) We will assess non-competent first sex for those reporting only same-sex intercourse via the other items but not assessing protection because this is primarily relevant for anal sex, which is extremely rare among this age group and according to our PPI is unacceptable to include in school surveys.(71) This primary outcome replaces pregnancy, which was the indicative primary outcome in the pilot RCT, because: pregnancy was judged too narrow a measure of sexual health; pregnancy is relevant only for girls and heterosexual sex; pregnancy does not reflect the areas of greatest sexual health need in terms of current trends; and powering a trial on this outcome would require an unfeasibly large school sample of >100 schools per arm.(46) Non-competence at first sex strongly predicts a range of subsequent adverse sexual health outcomes listed above, more so than is the case for other measures of early sexual-risk behaviour.(1, 2) The pilot RCT indicated good performance of the Natsal competence measure in terms of completion (88%) and inter-item reliability (ordinal alpha=0.74).

Secondary outcomes will examine other important potential benefits:

- age at sexual debut, using an adapted version of the RIPPLE measure;(72)
- non-use of contraception at first and last sex among those reporting heterosexual intercourse, using an adapted version of the RIPPLE measure;(72)
- number of sexual partners, using an adapted RIPPLE measure;(72)
- dating and relationship violence (DRV) victimisation (including non-volitional sex) measured using an adapted version of the short Conflicts in Adolescent Dating Relationships Inventory (sCADRI) scale which is widely used and was piloted for reliability in our recent Project Respect study (ordinal alpha=0.89);(42, 73, 74)
- sexually transmitted infections (STIs), focused on self-reported diagnosis with common infections, using an adapted version of the RIPPLE measure;(72)
- pregnancy and unintended pregnancy for girls and initiation of pregnancy for boys using adapted versions of the RIPPLE measures.(72)

*Intermediate outcome measures:* We will not undertake mediation analysis because this requires two waves of follow-up, which is not planned in the interests of minimising costs and maximising school retention. It is our experience across studies that multiple follow-ups reduce rather than maintain school engagement and hence response rates.(52) However, informed by our theory of change,(64, 65) we will undertake exploratory analyses of intervention effects on the following ‘intermediate’ outcomes(75) using existing measures(36, 39, 51, 76) tested for reliability in our pilot (ordinal alphas indicated below for multi-item scales): school-level social norms supportive of healthy relationships and sexual health (alpha=0.77); individual-level attitudes towards DRV (alpha=0.65) and gender roles (alpha=0.68); individual-level school engagement (alpha=0.74); career/educational aspirations; sexual health knowledge (alpha=0.78); sexual health and contraceptive skills (alpha=0.92); sexual communication self-efficacy (alpha=0.93); and communication with parents; sexual and reproductive health services access (alpha=0.83) DRV perpetration (including non-volitional sex) measured using sCADRI (ordinal alpha=0.88); and sexual harassment.(77)

*Economic outcomes:* Outcomes for the economic analysis will include the above primary and secondary outcomes. In addition, the Child Health Utility (CHU) 9D measure(78) will be used to assess student’s health‐related quality of life. The CHU‐9D is a validated age‐appropriate measure that was explicitly developed using children’s input and has been suggested to be more appropriate and function better than other health utility measures for children and adolescents.(79) This measure performed well in the pilot. Student utility values will be collected at baseline and at follow‐up surveys at 33 months using the CHU‐9D questionnaire.

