***Analytic sample and sample size***

We calculate that, for 80% power with 5% significance, conservatively assuming: a sample of 140 students per school; drop out of 2 schools per arm; 80% student survey response rate at follow-up; an intra-cluster correlation coefficient (ICC) of 0.015 for our primary outcome; and prevalence of this outcome of 9% among those in the control arm, we will require 25 schools per arm to detect a 36% reduction in the primary outcome (giving a prevalence of 5.85% in the intervention arm). The minimum analytic sample for outcome assessment in the RCT will therefore be approximately 6440 students providing follow-up data at 33 months. Repeating this power calculation for the originally intended primary outcome of conceptions (where the prevalence among female controls would be around 2%)(13) would require >100 schools per arm.

These estimates are informed by research and PPI. We assume 140 students per school informed by our recent INCLUSIVE trial.(52) This is a conservative assumption for the Positive Choices trial because the average year group has now risen to 190 and so assuming an 80% response rate (again informed by the Positive Choices pilot and previous studies(42, 52-54)) this would comfortably provide over 150 students.(55) Two schools dropping out is also a conservative assumption given our previous trials have experienced no drop outs.(42, 52, 53) Regarding ICCs, no data are available on school-level clustering of lack of sexual competence at first sex but we would expect this to be very similar to ICCs for non-use of contraception at first sex, which are reported as 0.01(56, 57) so a conservative assumption of 0.015 for this study is reasonable.

Our assumption about prevalence of the primary outcome among controls is also informed by the literature. Around 25% of 15-16 year-olds are sexually active compared with 7% of 12-13 year-olds.(58) Therefore, between baseline and follow-up, we would expect 18% of students to become sexually active. Data from young people participating in the third Natsal sexual behaviour survey suggest that, among those aged 15-16 years, around half lack sexual competence at first sex.(1, 2) Therefore, we would expect around half of trial participants who become sexually active by follow-up (i.e. 9% of all participants) will experience non-competent sexual debut.

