A statistical analysis plan will be drafted by the CTU and a data dictionary by the fieldwork team. Statistical analysis of survey data will be led by the CTU, with analysis of fidelity data by the fieldwork team and economic data by [name]. School randomisation and retention, and student response rates will be described using a CONSORT diagram.(88) Baseline and follow-up data will be tabulated by arm. Continuous outcomes will be summarised for each trial arm using means and standard deviations and binary outcomes will be summarised for each trial arm using numbers and percentages. We will conduct intention-to-treat analyses of primary and secondary outcomes (88) as well as exploratory analyses of our intermediate outcomes (RQ1) to estimate intervention effects, reporting 95% confidence intervals and P values for primary and secondary outcomes but not for exploratory analyses of the intermediate outcome. The analytic sample will be students providing follow-up data at 33 months. Analyses will account for school clustering. All outcomes will be analysed using generalised estimating questions (GEEs) with an exchangeable correlation structure and the sandwich estimator of variance to adjust for clustering, with small sample bias correction for the degrees of freedom. For binary outcomes GEEs will be fitted, with a log link to estimate risk ratios and identity link to obtain risk differences. In the event of low prevalence resulting in non-convergence of the GEE model a hierarchical modified Poisson regression model will be used to obtain risk ratios, followed by marginal standardisation to obtain risks for calculating risk differences where required. For continuous outcomes GEEs with an identity link will be used to obtain mean differences.

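### The primary outcome's denominator is unresolved: one section confines it to students with a post-baseline first sex, while the sample size and analysis sections use all students with follow-up data, and no coding rule links the two

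*Combined protocol and SAP*

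**What the plan says.** Under Outcome measures, the primary outcome is a binary measure of non-competent first sex, and "Non-competent first sex will be assessed among trial participants having sex for the first time between baseline and follow-up".

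Under Analytic sample and sample size, the control risk is built from 18% of students becoming sexually active between baseline and follow-up (25% minus 7%), about half of them without competence: "i.e. 9% of all participants) will experience non-competent sexual debut". The calculation assumes a "prevalence of this outcome of 9% among those in the control arm", a fall to 5.85% and a minimum of about 6440 students.

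Under Data management and analysis, "The analytic sample will be students providing follow-up data at 33 months". The sections Study population and Minimising bias define the sample in the same way. The first research question, Design, and the analysis and bias sections all describe the main analysis as intention-to-treat.

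A secondary outcome has a similar restriction: "non-use of contraception at first and last sex among those reporting heterosexual intercourse".

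**The concern.** These texts describe two estimands. One is the proportion of all students who have a non-competent first sex after baseline. The other is the proportion of post-baseline debuts that are non-competent. Two analysts following the plan faithfully could report different primary results.

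The second estimand also selects on something that happens after allocation. Baseline surveys precede randomisation, so a debut after baseline is almost wholly a post-randomisation event. The protocol treats debut as modifiable:

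- Age at sexual debut is a secondary outcome, listed among potential benefits.
- The Background cites whole-school interventions as delaying debut.
- Two of the three source interventions are cited for the same effect: Carrera (OR 0.52, among girls) and Gatehouse (OR 0.55).

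If the intervention changes who debuts, the debuting students in the two arms are no longer comparable groups. A debut-only proportion could then miss a real fall in the number of students who experience non-competent first sex.

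**Working it through.** **Inputs.** All are from Analytic sample and sample size unless marked as assumed.

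- "a sample of 140 students per school; drop out of 2 schools per arm; 80% student survey response rate at follow-up"; 25 schools per arm less 2 gives 23.
- "an intra-cluster correlation coefficient (ICC) of 0.015 for our primary outcome".
- Control risk 9%; intervention risk 5.85%. The stated 36% reduction gives 9% × 0.64 = 5.76%, so both values are shown.
- 18% debut between baseline and follow-up; about 50% of those debuts non-competent.
- Significance 5%; two-sided is assumed, because the plan does not say.

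**Formula.** Effective size per arm: n = students / [1 + (m − 1) × ICC], where m is students per school. Power = Φ(|p₁ − p₂| / SE − 1.96), with SE = √[p₁(1 − p₁)/n₁ + p₂(1 − p₂)/n₂].

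**Step 1: the plan's own figure.** 2 × 23 × 140 = 6440, which matches exactly and takes 140 as the students analysed per school. The design effect is 1 + 139 × 0.015 = 3.085, so n = 3220 / 3.085 = 1043.8 per arm.

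- 9% v 5.85%: SE = 0.01146, power 78.5%.
- 9% v 5.76%: power 81.0%.

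The stated 80% is reproduced with all students as the denominator.

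**Step 2: the literal debut-only denominator.** 6440 × 0.18 = 1159 students, or 140 × 0.18 = 25.2 per school. Control risk is 9 / 18 = 50%. The figures 9%, 5.85% and 6440 do not describe this analysis.

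**Step 3: the same 36% all-student reduction by three routes.** The route is assumed in each case. The ICC among debuting students is not given: 0.015 is carried over and 0.05 is an assumed alternative.

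| Route | Intervention-arm debut | Non-competent among debuts | All-student RR | Debut-only RR | Debut-only power, ICC 0.015 | ICC 0.05 |
|---|---|---|---|---|---|---|
| Better competence only | 18% | 32% | 0.64 | 0.64 | above 99% | 98.9% |
| Equal split (0.8 × 0.8) | 14.4% | 40% | 0.64 | 0.80 | 80.6% | about 62% |
| Fewer debuts only | 11.52% | 50% | 0.64 | 1.00 | 5% (= alpha) | 5% (= alpha) |

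In the equal-split row the intervention arm has 140 × 0.144 = 20.16 debuts per school against 25.2 in control. At ICC 0.015 the effective sizes are 579.6 / 1.363 = 425.2 and 463.7 / 1.287 = 360.2. Then SE = √(0.25/425.2 + 0.24/360.2) = 0.0354, and power = Φ(0.10/0.0354 − 1.96) = 80.6%.

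**Step 4: is the fewer-debuts route far-fetched?** Applying the Gatehouse OR of 0.55 to an 18% debut risk: odds 0.18/0.82 = 0.2195; × 0.55 = 0.1207; risk 0.1207/1.1207 = 10.8%. With half of debuts still non-competent, the all-student RR is 10.8/18 = 0.60. A debut effect of the size the protocol cites could by itself exceed the planned reduction. This is an illustration, not a forecast.

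**The case against.** The best defence is that the Outcome measures sentence only says who can answer the competence items, with everyone else scored 0. That reading fits the 9%, the 6440, the analytic sample and the intention-to-treat label. The same section also justifies the outcome by its prevalence among trial participants, which suits an all-student measure. The version history says that version 7.0 was aligned with a statistical analysis plan agreed in January 2023; no separate plan is in the supplied text, and the rule may be there. All of this stands as a reason not to assume the worst. It does not remove the conflict, because the all-student coding is nowhere written.

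Four stronger readings are tempting, and the documents do not support them.

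- *The primary analysis is certainly debut-only.* One sentence points that way; several sections point the other way.
- *The trial is underpowered.* The calculation is sound for an all-student outcome, and debut-only power is higher if only competence changes.
- *Delaying debut is the intervention's aim.* The stated aim is competence at first sex. Later debut is a listed potential benefit, and no debut effect is cited for Safer Choices.
- *A debut-only analysis would show harm.* This is arithmetically possible. If competent debuts fell from 9% to 5% and non-competent from 9% to 8%, the debut-only RR would be (8/13)/(9/18) = 1.23 against 8/9 = 0.89 for all students. But those inputs are chosen; nothing in the protocol suggests that mainly competent debuts would be prevented.

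**Conclusion.** The concern holds as an unresolved conflict in the primary estimand. The plan gives two denominators, about 1159 and 6440 students, with control risks of about 50% and 9%, and no rule for students never active or already active at baseline. The stated power belongs only to the larger one. The smaller one is not a randomised comparison and departs from the intention-to-treat analysis the plan promises.

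For the same planned effect, the debut-only risk ratio ranges from 0.64 to 1.00 depending on how the effect arises, so the choice can change the trial's conclusion. That range rests on the protocol's 18% and 50%, on assumed routes of effect, and on an ICC among debuting students that the plan does not give. The conflict itself rests on the text alone.

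**What to change.** In Outcome measures and in the statistical analysis plan:

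1. State that the primary outcome is analysed in all students with 33-month data: 1 for a first sex after baseline that was non-competent; 0 for never active, competent debut, or debut before baseline. The last group is in the denominator of the 9% already, at about 7% of students by the protocol's figures.
2. Add a sensitivity analysis excluding students who reported debut at the baseline survey, using actual baseline reports. Missing baseline debut age is to be imputed from follow-up answers, and Supplementary Material 4 shows 1667 of 6268 endline respondents unmatched to baseline. Status recalled at follow-up is not pre-randomisation data, and the plan should say so.
3. Label the proportion among debuting students as descriptive.
4. Report non-use of contraception per student alongside the version among those reporting intercourse, or label the latter a non-randomised comparison.
5. If analysis has begun (Supplementary Material 4 already gives endline counts), document which denominator was used and report both.

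The cost is wording and some extra output; no new data are needed. The one drawback is that the effect is expressed per student and not per debut.

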***Assessment and follow up***

Baseline surveys will be done before randomisation when students are in year 8 (age 12/13) in November 2021-March 2022 and will collect data on socio-demographic characteristics, sexual debut and other covariates, drawing on existing survey items.(80) Consent procedures are described under ethics below. Paper questionnaires will be completed confidentially in classrooms supervised by trained fieldworkers, with teachers remaining at the front of the class to maintain quiet and order, but unable to see student responses. Previous experience indicates that paper questionnaires are acceptable and logistically more straightforward than tablet surveys. We will survey absent students by leaving questionnaires and stamped addressed envelopes with schools, and liaising with schools to maximise returns. If schools do not allow face-to-face fieldwork visits, we will instead survey students using an online survey. This will involve students completing online surveys in classrooms supervised by teachers but with teachers remaining at the front of the class to maintain quiet and order, but unable to see student responses, and with fieldworkers available via telephone or internet technology to answer questions in real time. If schools dismiss classes and move to online learning because of Covid infections, we will offer schools the option of surveying students online at home. Schools will send students details of how to log in to surveys using laptops, phones or tablets. Surveys will include links to information boxes explaining key terms informed by the questions students have raised during classroom-based surveys. Students will be asked to skip questions they do not understand or do not wish to answer. Students will be advised to contact their school safeguarding lead for support should they feel confused or upset as a result of completing the questionnaire, with the team briefing safeguarding leads about this and liaising with them to record where this has occurred. We will resurvey students at 33 months (September-December 2024) as students begin year 11 (age 15/16) and will collect self-report data on socio-demographic characteristics, intervention reach/acceptability and outcomes. Survey fieldworkers, but not students, will be blind to allocation. Based on past studies and our pilot,(51, 72, 81) we expect at least 80% survey response rates at baseline and follow-up.

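### The contraception-at-first-sex secondary outcome has no time window, so as written it counts first-sex events before baseline, which dilutes its estimated effect

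*Combined protocol and SAP*

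**What the plan says.** Under Outcome measures, the secondary outcome is "non-use of contraception at first and last sex among those reporting heterosexual intercourse, using an adapted version of the RIPPLE measure". The only condition is on the type of intercourse; nothing is said about when first sex took place. In the same section the primary outcome does have a window: "Non-competent first sex will be assessed among trial participants having sex for the first time between baseline and follow-up".

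Data management and analysis does not supply the missing condition: "The analytic sample will be students providing follow-up data at 33 months". Study population and Minimising bias both provide for filling in missing baseline age of sexual debut from follow-up answers, but neither uses debut timing to restrict this outcome.

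The sample-size section relies on the distinction between earlier and later debut. It states "Around 25% of 15-16 year-olds are sexually active compared with 7% of 12-13 year-olds" and concludes that "between baseline and follow-up, we would expect 18% of students to become sexually active". Assessment and follow up places the baseline survey in year 8, before randomisation, and says that it "will collect data on socio-demographic characteristics, sexual debut and other covariates".

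**The concern.** Whether contraception was used at a first intercourse before the year-8 survey was settled before schools were allocated and before any lesson was taught. Such events are the same with or without the intervention. Counting them pulls the risk ratio towards 1 and adds variance.

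This matters because secondary outcomes are to be reported with confidence intervals and P values. Contraception is also one component of the primary composite. As written, the component and the composite cover overlapping but different sets of first-sex events. A weak contraception result beside a stronger primary result could then partly reflect the wider event set.

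**Working it through.** **1. The plan's own figures.** New debuts between the surveys: 25% − 7% = 18%. Half of these non-competent: 9%. Minimum sample: (25 − 2) schools × 2 arms × 140 = 6440. All three agree with the sample-size section.

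**2. Share of first-sex events before baseline.** 7/25 = 28%. In 6440 students that is 0.07 × 6440 ≈ 451 of 0.25 × 6440 = 1610 events, leaving 0.18 × 6440 ≈ 1159 after baseline. If the baseline share were 5% or 9% (assumption) with 25% at follow-up, the share would be 20% or 36%.

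**3. Dilution of the risk ratio.** Assume a ratio of 0.64 for debuts after baseline (the 36% reduction planned for the primary outcome) and the same control-arm non-use before and after baseline.

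- Analysed RR = (0.07 + 0.18 × 0.64)/0.25 = 0.1852/0.25 = 0.741, so a 36% reduction appears as 26%.
- With a 20% share: 0.20 + 0.80 × 0.64 = 0.71. With 36%: 0.36 + 0.64 × 0.64 = 0.77.
- If non-use were q times as common at early debuts (assumption), the early share of control-arm non-use events is w = 0.28q/(0.28q + 0.72), and RR = w + (1 − w) × 0.64. For q = 1.5, w = 0.37 and RR = 0.77. For q = 2, w = 0.44 and RR = 0.80.

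**4. Information lost.** Expected z = (p1 − p2)/√[(p1(1 − p1) + p2(1 − p2))/n_eff], with n_eff = n/[1 + (m − 1) × ICC], where n is students per arm and m is students per school in the denominator. Without restriction of the denominator, n = 23 × 140 = 3220 and m = 140. The ICC is 0.01 (the figure the plan reports for contraception non-use at first sex) or 0.015 (the figure used for the primary outcome). Non-use at first sex is assumed to be 10%, 20% or 30%. The gain in information is the squared ratio of the two z values, minus 1.

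Worked case: all students in the denominator, 20% non-use, ICC 0.01, so n_eff = 3220/2.39 = 1347.

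- With early events: p1 = 0.25 × 0.20 = 0.0500, p2 = 0.0500 × 0.7408 = 0.0370, z = 1.65.
- Without: p1 = 0.18 × 0.20 = 0.0360, p2 = 0.0360 × 0.64 = 0.0230, z = 1.99.
- (1.989/1.650)² = 1.45.

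| Denominator | z with early events | z without | Gain (this case) | Gain, non-use 10-30%, both ICCs |
|---|---|---|---|---|
| All students | 1.65 | 1.99 | 45% | 44-46% |
| All students before restriction; early debuts also leave the denominator after it | 1.65 | 2.03 | 52% | 51-54% |
| Only students reporting sex (805 per arm before, 580 after) | 2.38 | 2.98 | 58% | 57-63% |

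On the all-student denominator the absolute difference is the same in both versions (0.0130). There the gain comes from lower variance, and only the risk ratio, not the risk difference, is diluted. Among students reporting sex, both are diluted.

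**The case against.** The strongest reply concerns the remedy. It is tempting to say that early debuts are known from the baseline survey and can be removed without any risk of selection. The participant flow in Supplementary Material 4 does not support that: only 4601 of 6268 endline respondents (73.4%) were matched to a baseline response, and 1667 (about 27%) were not. For unmatched students the plan's route is age at debut reported at follow-up. That report comes after randomisation, from students who are not blind to allocation. The exclusion is strictly pre-randomisation only where debut was recorded at baseline. This objection stands and shapes the fix. It does not remove the point, because the primary outcome needs the same classification of debut timing.

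The denominator is also unsettled. The item's wording points to students reporting heterosexual intercourse. For the primary outcome, Outcome measures speaks of those with first sex in the interval, while the sample-size section counts 9% of all participants. Hence a range of gains, not one figure. The direction is the same on every denominator tried.

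The 28% is a planning expectation. It comes from literature prevalences of being sexually active in two age groups, not from heterosexual debut observed in this cohort.

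A reader might infer that the contraception result is systematically biased, or that it cannot help to interpret the primary result. Neither follows. Early events should balance between arms, and on the planning figures 72% of first-sex events fall after baseline. The protocol also presents the secondary outcomes as further benefits, not as a breakdown of the composite.

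Finally, the Version control table says version 7.0 was aligned with a statistical analysis plan agreed in January 2023. No separate text of that plan is in the document reviewed. A window may be stated there; if so, the outcome list should carry it.

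**Conclusion.** The point holds for the first-sex half of one secondary outcome. The text sets no window, so following it counts events that the intervention cannot affect: about 28% of first-sex events on the planning figures, with a plausible range of 20% to 36%.

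The consequence is dilution and lost precision. An assumed true ratio of 0.64 would be seen as about 0.74, or up to 0.80 if non-use is twice as common at early debuts. Restricting to debuts after baseline gives roughly 45% to 60% more information. These sizes rest on a ratio borrowed from the primary outcome, on assumed non-use of 10% to 30%, and on being sexually active as a proxy for heterosexual debut. The primary analysis is unaffected, and dilution of this kind does not create false positives. The change is worth making because it is cheap and uses a classification the trial already needs.

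**What to change.** - Define the first-sex half as non-use of contraception at a first heterosexual intercourse occurring after baseline, with the same rule for classifying debut timing as the primary outcome. Leave the last-sex half unchanged.
- State the denominator explicitly.
- Use debut reported at baseline where it exists. For students without a matched baseline record, use age at debut reported at follow-up, as Study population and Minimising bias already provide.
- Add a sensitivity analysis limited to students with debut recorded at baseline.
- Report the unrestricted version descriptively.

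The cost is a few sentences in the outcome list and analysis plan and one extra analysis; no new data are needed. The downsides are fewer events and some misclassification of debuts close to the baseline survey.
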